## Abstract

**Background:**

The shortage of organs for kidney transplantation for patients with end-stage renal disease (ESRD) is magnified in Hispanics/Latin Americans in the United States. Living donor kidney transplantation (LDKT) is the treatment of choice for ESRD. However, compared to their representation on the transplant waitlist, fewer Hispanics receive a LDKT than non-Hispanic whites. Barriers to LDKT for Hispanics include: lack of knowledge, cultural concerns, and language barriers. Few interventions have been designed to reduce LDKT disparities. This study aims to reduce Hispanic disparities in LDKT through a culturally targeted intervention.

**Methods/Design:**

Using a prospective effectiveness-implementation hybrid design involving pre-post intervention evaluation with matched controls, we will implement a complex culturally targeted intervention at two transplant centers in Dallas, TX and Phoenix, AZ. The goal of the study is to evaluate the effect of Northwestern Medicine’s® Hispanic Kidney Transplant Program’s (HKTP) key culturally targeted components (outreach, communication, education) on Hispanic LDKT rates over five years. The main hypothesis is that exposure to the HKTP will reduce disparities by increasing the ratio of Hispanic to non-Hispanic white LDKTs and the number of Hispanic LDKTs. We will also examine other process and outcome measures including: dialysis patient outreach, education session attendance, marketing efforts, Hispanic patients added to the waitlist, Hispanic potential donors per potential recipient, and satisfaction with culturally competent care. We will use mixed methods based on the Promoting Action on Research Implementation in Health Services (revised PARIHS) and the Consolidated Framework for Implementation Research (CFIR) frameworks to formatively evaluate the fidelity and innovative adaptations to HKTP’s components at both study sites, to identify moderating factors that most affect implementation fidelity, and to identify adaptations that positively and negatively affect outcomes for patients.

**Discussion:**

Our study will provide new knowledge about implementing culturally targeted interventions and their impact on reducing health disparities. Moreover, the study of a complex organizational-level intervention’s implementation over five years is rare in implementation science; as such, this study is poised to contribute new knowledge to the factors influencing how organizational-level interventions are sustained over time.

**Trial registration:**

(ClinicalTrials.gov registration # NCT03276390, date of registration: 9–7-17, retrospectively registered)

## Background

More than 600,000 patients in the U.S. have end-stage kidney disease (ESRD) for which dialysis or transplantation are the only life-saving options [1]. Disproportionately more ESRD patients are Hispanics/Latin Americans (“Hispanics”) than non-Hispanic whites [1], which contributes to the greater demand for kidney transplantation. Thus, while the shortage of kidneys for transplantation adversely affects all patients with ESRD, the shortage is accentuated for Hispanics [2, 3]. In 2016, disproportionately fewer waitlisted Hispanics than non-Hispanic whites received kidney transplants: 17.8% versus 25.1% [4], despite having a disproportionately higher prevalence of ESRD [1, 5–8]. Living donor kidney transplant (LDKT) is the optimal treatment for ESRD as it engenders longer patient and graft survival, shorter waiting time, and better quality of life than deceased donor kidney transplantation [9–12]. Further, transplantation is more cost-effective than dialysis [1]. However, in 2016, disproportionately fewer waitlisted Hispanics than non-Hispanic whites received a LDKT: 4.6% versus 10.5% [13]. This disparity will likely worsen without a change in current medical practice as Hispanics are the largest and fastest growing ethnic minority group in the United States (U.S.) [14, 15].

Barriers to LDKT specific to Hispanics are due to: misconceptions about living kidney donation (LKD), fears about not being able to have children, fears about shortening the donor’s life expectancy [16], lack of educational materials about transplantation in Spanish [17, 18], concerns over legal documentation, and preferences for “high context communication” [19] or education provided through face-to-face and group settings [16, 18, 20]. Hispanics also maintain concerns about LDKT that other groups have expressed, including: lack of knowledge about LKD [8, 18, 21–24], fear of surgery [16, 21, 23], financial concerns [18, 23, 25, 26], distrust of healthcare providers [19, 21, 23], recipient reluctance to request donation [23, 25, 27], and patients’ refusal of living donation out of concern for donor well-being [23].

Culturally competent or targeted interventions have contributed to the reduction in health disparities [28–30]. Cultural competency pertains to: “A set of values, principles, behaviors, attitudes, policies, and structures that enable organizations and individuals to work effectively in cross-cultural situations.” [31]. A feature of cultural competency is cultural congruence, which refers to: “those cognitively based assistive, supportive, facilitative, or enabling acts or decisions that are tailor made to fit with individual, group, or institutional cultural values, beliefs, and lifeways in order to provide or support meaningful, beneficial, and satisfying health care or well-being services” [32] and occurs when patients and providers share the same ethnic background, cultural beliefs, and values. Both concepts rely on the concept of “culture,” defined as: “a generalized, coherent context of shared symbols and meanings that persons dynamically create and recreate for themselves in the process of social interaction… culture is something people come to take for granted...” [33] Linguistic congruence entails: “The capacity of an organization and its personnel to communicate effectively, and convey information in a manner that is easily understood by diverse audiences including persons of limited English proficiency, those who have low literacy skills or are not literate…” such as through bilingual/bicultural or multilingual/multicultural staff [34]. National Standards for Culturally and Linguistically Appropriate Services in Health Care were designed to reduce disparities in healthcare delivery and to help healthcare systems better address patients’ needs.

Healthcare organizations and providers have a responsibility to reduce racial/ethnic disparities in health to improve equity, and by embedding interventions into their quality improvement initiatives [35]. The Robert Wood Johnson’s Finding Answers: Disparities Research for Change program identified best practices for implementing interventions into healthcare settings to reduce health disparities, including: “1) Recognize disparities and commit to reducing them, 2) Implement a basic quality improvement structure and process, 3) Make equity an integral component of quality improvement efforts, 4) Design the intervention(s), 5) Implement, evaluate, and adjust the intervention(s), 6) Sustain the intervention(s).”

A few culturally competent interventions (e.g., combined home and transplant center education, public awareness campaigns, and patient/family communication with social workers) have been shown to increase LDKT rates [36–42]. Studies also show that increasing knowledge about LDKT increases potential donors’ willingness to donate, living donor inquiries with transplant centers, donor evaluations, and actual LDKTs [39, 43, 44]. Most interventions focus on African Americans [40, 41], [44–46]. Few interventions target Hispanics’ cultural concerns [36] by raising awareness of living donation as a treatment option [21] and increasing willingness to become a living donor via mass media campaigns [21, 42]. Because disparities in minority access to LDKT can be attributed to provider and hospital level factors (e.g., lack of minority healthcare providers, or language or literacy-appropriate educational materials) [47], interventions are needed at the transplant center level. No studies have assessed the effectiveness of culturally competent transplant center-based interventions to increase LDKT in Hispanics. Additionally, none of these interventions have evaluated the implementation of their intervention.

Despite the increasing value placed on improving equity in healthcare organizations, systematic reviews of interventions designed to reduce racial/ethnic disparities in other conditions (e.g., HIV prevention [48], cervical cancer screening, diagnosis, and treatment [49], prostate cancer treatment decision making [50], colorectal care [51], asthma outcomes [52]) found that few interventions entailed culturally targeted components, and that few interventions targeted changing health provider behavior or organizational microsystems [35]. Moreover, few implementation studies designed to reduce ethnic/racial disparities have evaluated the fidelity of their intervention implementation [53, 54].

The implementation science literature has also witnessed a paucity of complex longitudinal interventions at the organizational level that have been evaluated for their implementation [55]. Complex interventions generally involve multiple interacting components, multiple people delivering the intervention, with those delivering the intervention engaging in many and/or difficult behaviors, multiple organizational levels, relatively little flexibility is permitted in tailoring the intervention, and multiple and/or diverse outcomes [56]. Few implementation studies are prospective [57] and even fewer focus on organizational-level interventions [55]. Both complex and multi-year long interventions can make the implementation process more difficult to initiate and sustain, and thereby jeopardize the intervention fidelity and outcomes. Understanding which kinds of complex intervention components are more or less feasible to implement, and how the intervention duration can influence sustainability, are important factors that require further attention.

This protocol describes a theory-driven study to evaluate the effectiveness of the Northwestern Memorial™ Hispanic Kidney Transplant Program as a complex, longitudinal, culturally targeted intervention to increase living kidney donor transplantation among Hispanics, and to ultimately reduce health disparities in kidney transplantation. The specific aims of the study are as follows:

### Specific aims

Aim 1. To implement the HKTP at two transplant centers by conducting a needs assessment of barriers and using a “learning collaborative” model to deliver HKTP protocols, scripts, and materials.

Aim 2. To evaluate how factors from the CFIR and the Revised PARIHS frameworks, and emergent factors unique to the implementation of culturally competent care, affect fidelity.

Aim 3. To conduct a pre-post HKTP intervention evaluation with matched controls to evaluate the effect of the HKTP, and the influence of innovation adaptations, on intermediate and final outcomes.

### Conceptual framework

The revised version of the Promoting Action on Research Implementation in Health Services (Revised PARIHS) [58, 59] and the Consolidated Framework for Implementation Research (CFIR) will be used in both implementation design and testing. Although the CFIR is more comprehensive than any single framework because it comprises nineteen other theories and frameworks [60], it does not include facilitation from the revised PARIHS. From these frameworks, we have identified core concepts that will be used to compare the two transplant centers implementing the HKTP. Successful implementation entails the development of an implementation plan and its realization, the uptake of evidence-based innovation, and the achievement of patient and organizational outcomes [61]. We will examine which of the following factors influence the successful implementation of the HKTP.

**Evidence** focuses on the knowledge of, clinical expertise in, patient preferences for, and relative advantage of the evidence-based practice [59]. The Revised PARIHS framework and the CFIR both argue that settings which have some knowledge of the research supporting the intervention (i.e., cultural differences underlying differential rates of Hispanic LDKT rates), clinical evidence of outcomes (i.e., increased Hispanic LDKT rates), and have patients who show a preference for the intervention will be more likely to successfully implement the intervention.

**Relative advantage** focuses on perceived comparative benefit of the HKTP to current practice for promoting living kidney transplantation. The CFIR argues that sites that perceive the intervention as providing a greater relative advantage will be more likely to implement the protocol with fidelity.

**Complexity** describes the perceived difficulty of implementing the HKTP. The CFIR argues that this perception varies depending on how many processes and practices needed to be reoriented or changed in order to implement the protocol, and as such, varies from context to context.

**Perceptions of the quality & packaging, costs, and adaptability of the protocol** describes several factors from the CFIR that refer to individuals’ perceptions of interventions. These perceptions, irrespective of the objective characteristics of the HKTP, shape willingness to implement the intervention.

**Outer setting** refers to the broader economic, political, and social contexts in the CFIR. Factors from the outer setting, including the degree to which knowledge of patient needs and resources are accurately known, the degree of cosmopolitanism, peer pressure, and external policies and incentives, influence the likelihood of a successful implementation.

**Inner setting** refers to structural, political, and cultural contexts (e.g., communications between transplant staff) through which the implementation process unfolds within the organization [62]. In particular, we examine the role of structural characteristics, culture, implementation climate, and contextual readiness of the transplant center.

**Facilitation** refers to a process of “helping individuals and teams to understand what they need to change and how they need to change it in order to apply evidence to practice.” [58, 63]. The facilitator, or ‘change agent,’ will provide help, guidance, and support to change attitudes, habits, skills, and ways of thinking and working in order to successfully implement the intervention [64]. In the Revised PARIHS framework, facilitation takes a central role. As such, we pay particular attention to how facilitation differences may influence implementation.

**The Cultural Competency Analytic Framework** will be used to guide the evaluation of the effectiveness of the HKTP on increasing culturally competent care, as evidenced by the increased number of LDKTs and increased patient satisfaction with care (Fig. 1) [65]. According to the framework, culturally competent healthcare system interventions (e.g., bicultural, bilingual staff) contribute to intermediate outcomes (e.g., less patient-provider miscommunication, increased patient understanding of treatment recommendations, increased patient satisfaction), which leads to improvements in health outcomes (e.g., increased number of LDKTs).

**Fig. 1 Fig1:**
[figure not shown]
Analytic Framework to Evaluate the Effectiveness of Healthcare System Interventions to Increase Cultural Competence (Adapted from [65])

## Methods and design

### Setting

The HKTP will be prospectively evaluated at two intervention sites: Baylor University Medical Center (BUMC) in Dallas, TX, and the Mayo Clinic in Phoenix, AZ. Both sites are located in cities serving the largest U.S. Hispanic (Dallas: 38.3%; Phoenix: 40.8%) and ethnic subgroup (Mexican) populations [66]. Intervention sites are matched with control sites by city population size, Hispanic proportion of the city population, and KT and LDKT volumes, including: Houston Methodist in Houston, TX (matched to BUMC), and University of Colorado Denver in Denver, CO (matched to MC). Control sites were selected in different cities than intervention sites to avoid contamination from local implementation efforts. As Northwestern Memorial Hospital (NMH)/Northwestern Medicine® (NM®) created the HKTP, but did not prospectively evaluate it, NMH/NM serves as the Study Coordinating Center. NMH/NM® is a nationally-recognized, academic teaching hospital, and includes one of the nation’s leading transplant centers.

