#### Community engagement

Outreach to the community is vital for increasing the number of patients referred to the HKTP. Bilingual/bicultural outreach staff (e.g., social workers) will hold 3 to 4 “lobby days” at dialysis centers per month. This will entail setting up a booth in the lobby to educate dialysis patients in Spanish about transplantation, address questions, and invite patients to come to the HKTP for transplant evaluation. The outreach staff will give patients materials describing the HKTP written in Spanish and English. When patients express interest in transplantation, the outreach staff will obtain patients’ contact information and hand out their business card. Upon returning to the transplant center, the outreach staff will enter a note in the transplant scheduling database and/or call patients back to confirm interest. The note in the database will trigger an email to the scheduler to call the patient to schedule an appointment.

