### Outcome measures

We will assess the reduction in disparities between self-identified Hispanics and non-Hispanic whites in LDKT rates for adult-to-adult living kidney donation. The effectiveness of the HKTP will be assessed by comparing the outcomes before introducing the HKTP and after the HKTP has been fully implemented. Measures will be collected at intervention and control sites in pre and post periods. For the final outcome measures, de-identified, aggregate center-level data will be collected from the Organ Procurement and Transplant Network/United Network for Organ Sharing (OPTN/UNOS) as publically reported data (Table 2). Data from sites’ medical record review will also be collected. Intermediate outcome measures about each Hispanic and non-Hispanic white potential recipient and potential donor will be collected monthly by research directly from intervention and control sites by medical record review to assess the pathways by which the HKTP potentially increases rates of Hispanic LDKT. We expect that the pre-post change will demonstrate a higher number of potential donors who initiate evaluation and complete more steps in the donor evaluation process.

**Table 2 Tab2:** Final and Intermediate outcome measures: transplant center-reported

Construct	Measure description
Final outcomes	
Ratio of Hispanics to Non-Hispanic Whites Receiving LDKTs	This ratio takes into account growth in transplant center volume while also providing a comparison to non-Hispanic whites, necessary for assessing disparities in LDKT [102]. The ratio provides an index of whether the Hispanic LDKT increase has grown over and above the increase observed at a center overall. By using this ratio, factors related to the center’s infrastructure and capacity to perform additional LDKTs that affect both Hispanics and non-Hispanic whites equally are accounted for. Institutional commitments to LDKT that are associated with higher rates of LDKT, can influence willingness to donate or preferences for LDKT, and affect both populations equally (e.g., paired donation, and desensitization efforts), are accounted for.
Number of Hispanic LDKTs	Change in number of Hispanic LDKTs compared to change in number of non-Hispanic white LDKTs will provide evidence that the increase is not at the expense of white patients.

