Number of Hispanic Patients Added to the Waiting list:	An increase in this number indicates success in overcoming barriers in gaining access (referral) to transplantation and completing the evaluation [103].
Number of Hispanic Potential Donors per Potential Recipient	An increase in this proportion reflects success in encouraging more potential living donors to undergo donor evaluation.
Intermediate Outcomes	
# Patients referred by outreach	The aggregate number of patients who were referred by outreach staff. Referral can be made by self, staff at dialysis centers, nephrologists, primary physicians, or transplant outreach staff.
# Patients scheduled/attending the education session	The aggregate number of patients who were scheduled and attended the HKTP education sessions.
# Patients who completed evaluation	The aggregate number of patients who completed the transplant evaluation process.
# Patients waitlisted	The number of additions to the transplant center’s own waiting list will serve as a proxy for access to the waiting list.
# Days on waiting list, dialysis time	The number of days patients have waited on the waiting list to date.
# Pre-emptive transplants	The number of patients who received a living donor transplant prior to going on dialysis.
# Potential donors at each phase of evaluation	The aggregate number of potential living donors who have completed each phase of the donor evaluation process.
# Days for donor to complete each phase of evaluation	The number of days from start to finish of each phase of living donor evaluation from initiation to clearance for donation to donation.
Potential donor disposition	The donor’s evaluation status as: initiated, completed, ruled out, withdrew, alternate donor found.
Contextual Outcomes	
Patient and potential donor socioeconomic status	Age, gender, race/ethnicity, insurance.
Organ Procurement Organization and transplant center factors	ESRD incidence, and transplant center volume.

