### Statistical analysis plan

SAS version 9.4 (Carey, NC) will be used for analyses. Testing of each hypothesis will be performed separately for each study site. For Hypotheses 1 and 2, quarterly UNOS outcome data (6 years pre- and 3.5 years post-HKTP) will be used to model ethnic and racial differences in transplants, to account for external events that could alter LDKT rates, and to analyze the sustainability of the HKTP intervention. Hypotheses 3 and 4 will be evaluated with monthly data. Associations between final outcome and intermediate outcome measures, and individual patient and donor level variables will be evaluated. Matched intervention and control sites will be compared.

To test hypothesis 1, we will use OPTN/UNOS data, to construct the ratio of the number of Hispanics receiving LDKTs to the number of non-Hispanic whites receiving LDKTs for each center from 6 years prior to 3.5 years after implementation of the HKTP. An interrupted time series (ITS) design with segmented regression analysis will be used to assess the HKTP. Ratio data will be collected across 24 quarterly time points pre-intervention (reference point), and 14 time periods post-intervention for a total of 38 time-series data points for each center.

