## Discussion

This research has the potential to make several important contributions to implementation science. First, the HKTP is a complex intervention targeted at the organization-level. Most implementation science research on changing healthcare professionals’ behavior has focused on changing an individual’s behavior rather than changing a healthcare organization [55]. As such, this research will uniquely examine the degree to which the CFIR and revised PARIHS frameworks describe the factors that influence the implementation of this type of intervention.

Second, this research examines the long-term implementation of the HKTP, with five years of observations. As such, it contributes to sparse research on how organizations sustain complex interventions over time [99].

Third, this research uniquely examines the implementation of an intervention focusing on reducing healthcare disparities. As such, it has the potential to expand the factors described in the CFIR framework. Specifically, this research will draw attention to how healthcare professionals’ perceptions of different patient groups may impact the implementation of the protocol.

Finally, this research uses an effectiveness-implementation hybrid design to examine both the antecedents to implementation fidelity and its outcomes [70]. In particular, this research is poised to explain both the factors that led to particular types of modifications to the design and the impact of those modifications on patient outcomes [91].

This study will advance knowledge of implementation science of culturally targeted interventions. Given that Hispanics comprise the largest and fastest growing minority population in the U.S. [14, 15], and are at disproportionately higher risk of ESRD requiring transplantation, [100] this study is expected to have a substantial and sustained impact on reducing health disparities in Hispanics. To our knowledge, the HKTP is the only culturally competent transplant program in the U.S. that upholds National Standards for Culturally and Linguistically Appropriate Services [101]. By implementing and evaluating the HKTP at other transplant centers, we expect to significantly increase LDKTs in Hispanics, and thereby save lives and improve the health of patients by leaving dialysis sooner and increasing pre-emptive KT. As participating transplant centers are located in two different geographic regions, the generalizability of study findings will be enhanced.

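### H1 and H2 are counted per study centre, so they cannot tell additional Hispanic LDKTs or listings from ones moved from other local centres

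*Protocol article*

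**What the plan says.** All references are to the protocol article.

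- **Unit of the outcome.** Under Outcome measures, for the final outcomes, "de-identified, aggregate center-level data will be collected from the Organ Procurement and Transplant Network/United Network for Organ Sharing". The same section says "Measures will be collected at intervention and control sites in pre and post periods". Under Statistical analysis plan, the H1 ratio is built "for each center from 6 years prior to 3.5 years after implementation of the HKTP", and H2 uses the same quarterly source.
- **Waiting list.** Table 2 reads a rise in Hispanic additions (a final outcome) as success in overcoming barriers to access. Its intermediate waiting-list row says that additions to the centre's "own waiting list will serve as a proxy for access to the waiting list".
- **Comparators.** Under Setting, each intervention site has one matched control: Houston for Dallas and Denver for Phoenix. The reason given is "Control sites were selected in different cities than intervention sites to avoid contamination from local implementation efforts".
- **Recruitment.** Under Community engagement, outreach staff at dialysis centres "invite patients to come to the HKTP for transplant evaluation". Table 1, Care delivery and supporting mechanisms, and Marketing add letters to referrers, in-service talks to local nephrology and social work groups, and Spanish-language media.
- **Intended conclusion.** Under Discussion: "By implementing and evaluating the HKTP at other transplant centers, we expect to significantly increase LDKTs in Hispanics".

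**The concern.** The intervention works partly by attracting Hispanic patients to a named centre, and the outcome is what happens at that centre. Two processes give the same signal. In one, patients who would not have been listed or received an LDKT now do so. In the other, patients who would have been listed or transplanted elsewhere locally now go to the HKTP. Only the first increases Hispanic LDKTs or improves access, which is what the article says it expects to show.

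The article already checks for one kind of displacement: Table 2 compares the change in Hispanic LDKTs with the change in white LDKTs, to show that the gain is not at white patients' expense. It describes no parallel check that the gain is not Hispanic LDKTs moved from another centre. The limitations in the Discussion mention spill-over to white patients but not movement between centres.

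**Working it through.** **The plan's own figure.** 6 years × 4 = 24 quarters before and 3.5 years × 4 = 14 after, total 38 per centre. This reproduces. The article gives no LDKT counts for any centre or city, so all volumes below are assumptions.

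**Do the described safeguards remove diversion?**
- *White denominator.* Table 2 claims protection against factors that affect both groups equally. Diversion through Spanish-language outreach is specific to Hispanic patients, so it enters the numerator only.
- *Distant controls.* Diversion around Dallas or Phoenix does not touch Houston or Denver, so the contrast passes it through in full.
- *Regional adjustment.* It uses the same matched controls.
- *Probabilistic sensitivity analysis.* It asks whether a change in volume at study sites is due to the HKTP. A diverted case is due to the HKTP, so it would pass.
- *Contextual measures.* ESRD incidence and centre volume do not count Hispanic LDKTs at other local centres.

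**Illustration 1: diversion only, no extra LDKT anywhere.** Let the intervention centre do H Hispanic and W white LDKTs a year, the other local centres HO and WO, and let a share d of HO move.

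Centre ratio: from H/W to (H + d·HO)/W. Area ratio: (H + HO)/(W + WO), unchanged.

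| H/W | HO/WO | d | Centre ratio | Change | Area ratio |
|---|---|---|---|---|---|
| 10/40 | 20/60 | 10% | 0.250 → 12/40 = 0.300 | +20% | 30/100 = 0.300 |
| 10/40 | 20/60 | 25% | 0.250 → 15/40 = 0.375 | +50% | 0.300 |
| 10/40 | 20/60 | 50% | 0.250 → 20/40 = 0.500 | +100% | 0.300 |
| 10/40 | 10/40 | 10%, 25%, 50% | 0.250 → 0.275, 0.312, 0.375 | +10%, +25%, +50% | 20/80 = 0.250 |
| 20/60 | 20/60 | 10%, 25%, 50% | 0.333 → 0.367, 0.417, 0.500 | +10%, +25%, +50% | 40/120 = 0.333 |

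Against a distant control with no change, the ratio of ratios is 1.10 to 2.00.

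**Would a same-city comparator help?** No. It loses what the intervention centre gains. In the second row its own ratio falls from 20/60 to 15/60, a factor of 0.75, so the ratio of ratios becomes 1.50/0.75 = 2.00. Over all rows it runs from 1.22 to 4.00.

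**Illustration 2: a fixed centre gain, with a varying diverted share f.** The centre's Hispanic LDKTs rise from 12 to 18 a year, (18 − 12)/12 = +50%. Other local centres do 12. Area change = 6(1 − f)/24: +25% at f = 0, +12.5% at f = 0.5, 0% at f = 1. The centre result is +50% each time.

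**Could the area series serve as a significance test?** Take f = 0, 6 years before, 3.5 years after, and simple Poisson counts without trend.
- Centre: 72 and 63 events. z = ln(1.5)/√(1/72 + 1/63) = 0.405/0.173 = 2.35; power about 65% (two-sided 5%).
- Area: 144 and 105 events. z = ln(1.25)/√(1/144 + 1/105) = 0.223/0.128 = 1.74; power about 41%.

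On these counts, a real and wholly additional effect would more often than not miss significance at area level.

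**The case against.** - **Control placement.** A reader might infer that putting controls in other cities is the fault. The documents do not support that. It guards against contamination, and a same-city comparator would enlarge the bias.
- **Where outcomes are counted.** A reader might infer that outcomes are counted at the intervention centre alone. They are also collected at the control centres. What is missing is any count for other centres in the intervention cities.
- **Size.** The article does not say how many other transplant centres serve Dallas or Phoenix, what they do, or how many patients could move. This stands: the figures show direction only.
- **Route.** Letters to referring practices may reach groups that already refer to the centre. The scheduling script, education sessions, wrap-up visit and follow-up of incomplete evaluations act on patients already in contact with it. Nothing says that patients met at lobby days were headed elsewhere. This makes full diversion unlikely, but does not rule out partial diversion.
- **Other evidence.** A reader might infer that a positive H1 or H2 would be worthless. That is too strong. It would show a centre-level gain, and the pathway measures and H3 bear on how it arose. Extra patient volume alone does not raise potential donors per potential recipient. The help is partial, because diverted patients could bring donors with them.
- **Condensed article.** An area analysis may exist in a fuller document. But the article itself fixes the outcome unit, the sites and the intended conclusion, and the point concerns how those fit together.

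**Conclusion.** The point holds as one about inference. H1 and H2 as defined can show that a study centre gained Hispanic LDKTs or listings. By themselves they cannot show that Hispanic LDKTs or access increased in the population served, and no analysis described in the article separates the two. The direction of the bias does not depend on the assumed volumes: any diverted case inflates the centre result in favour of the HKTP.

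Its size cannot be derived from the article. The 10% to 100% range rests on assumed centre volumes and on 10% to 50% of other local centres' Hispanic LDKTs moving. If no other centre serves the city, or no patient moves, the bias is zero. The documents give no evidence that diversion will occur, only that the design could not detect it through H1 or H2.

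**What to change.** Keep the centre-level series as the primary analysis and keep the distant controls. Then:

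1. From the same public OPTN/UNOS source, prespecify a supporting quarterly series of Hispanic and non-Hispanic white LDKTs and waiting-list additions, summed over all centres in the same city or Organ Procurement Organization area, for each intervention and control site.
2. Report its estimate and confidence interval beside the centre result.
3. Show the Hispanic series for the other local centres separately. A fall there when the HKTP starts would point to redistribution.
4. Do not require the area series to reach significance; the Poisson check shows why.
5. Word a positive result as a centre-level gain, with possible redistribution stated as a limitation, unless the area data support a net increase.

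The cost is one further extraction from a source already in use and a little more analysis. The area estimate is also diluted and less precise. In Illustration 2 with no diversion, +50% becomes +25%. The same 6 extra LDKTs a year carry a Poisson standard error of √(24/6 + 30/3.5) = 3.55 at area level, against √(12/6 + 18/3.5) = 2.67 at the centre. This is why the area series should support the primary analysis and not replace it.
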